## Abstract

**Background:**

New treatment strategies are required against infections caused by *Helicobacter pylori,* which grows increasingly resistant to antibiotics. Polymerase chain reaction-based methods for antibiotic susceptibility testing are available for detecting *H. pylori*-specific mutations that confer resistance to clarithromycin and levofloxacin. Several meta-analyses have compared eradication rates for susceptibility-guided versus empirical therapy for *H. pylori* treatment; however, all have significant limitations and high heterogeneity, and the results are contradictory. The main objective of this trial is to assess whether a sequential strategy based on molecular susceptibility testing-guided therapy for *H. pylori* has a better eradication rate than empirical therapy.

**Methods:**

This trial is designed as a prospective, randomised, open-label, active-controlled and single-centre study. Men and women who are *H. pylori*-positive, naïve to treatment, and aged 18–65 years will be recruited. A total of 500 participants will be randomised to receive either empirical therapy or a susceptibility-guided sequential strategy. Bismuth quadruple therapy will be the empirical first-line therapy, and in case of failure, high-dose dual (proton-pump inhibitor + amoxicillin) treatment will be the rescue therapy. For the susceptibility-guided sequential strategy, regimen selection will be based on *H. pylori* susceptibility to clarithromycin (first-line) and levofloxacin (rescue). A first-line treatment of clarithromycin triple therapy will be selected for clarithromycin-sensitive strains. For clarithromycin resistance, a high-dose dual therapy will be selected. During the rescue treatment, a levofloxacin quadruple regimen will be selected for levofloxacin-sensitive strains, and a furazolidone quadruple regimen will be selected for others. The primary outcome is the first-line eradication rate in both groups, and the overall (including first and rescue therapies) *H. pylori* eradication rate in both groups is one of the secondary outcomes. The eradication rates of *H. pylori* will be analysed by intention-to-treat analysis, modified intention-to-treat analysis, and per-protocol analysis.

**Discussion:**

This randomised controlled trial will provide objective and valid evidence about the value of polymerase chain reaction-based molecular methods for antibiotic susceptibility testing in guiding *H. pylori* eradication.

**Trial registration:**

Clinicaltrials.gov NCT05549115. Released on 18 September 2022. First posted on 22 September 2022. Enrolment of the first participant on 20 September 2022. The study is retrospectively registered.

**Supplementary Information:**

The online version contains supplementary material available at 10.1186/s13063-023-07457-z.

## Administrative information

Note: The numbers in curly brackets in this protocol refer to the SPIRIT checklist item numbers. The order of the items has been modified to group similar items (see http://www.equator-network.org/reporting-guidelines/spirit-2013-statement-defining-standard-protocol-items-for-clinical-trials/).

## Introduction

### Background and rationale {6a}

The pooled *Helicobacter pylori* prevalence is 44.2% (95% confidence interval [CI] [43.0–45.5]) in China, where approximately 589 million individuals are infected with *H. pylori* [1]. *H. pylori* infection is an infectious disease with an indication for antimicrobial therapy [2]. Only a few antibiotics (such as amoxicillin, clarithromycin, metronidazole, tetracycline, levofloxacin, and rifabutin) can be effectively used for the eradication of *H. pylori* in clinical practice. These treatments comprise combination therapies constituting two or three antibiotics, an acid inhibitor, and/or a bismuth component that provides additional antibiotic effects [3]. However, the increasing resistance of *H. pylori* to antibiotics has become a great concern. In a large study conducted in the US and Europe, of 907 participants, 22.2% were resistant to clarithromycin, 1.2% to amoxicillin, and 69.2% to metronidazole [4]. The resistance of *H. pylori* to antibiotics has decreased the eradication rate and caused treatment failure. For example, clarithromycin resistance was found to be significantly associated with the failure of clarithromycin-containing regimens (odds ratio: 6.97; 95% CI [5.23–9.28]; *P* < 0.001) [5]. This situation highlights the need for antibiotic resistance surveillance and the challenge of choosing optimised antibiotics based on antibiotic susceptibility testing (AST).

According to the map of antibiotic resistance of *H. pylori* in China—released by the Institute for Infectious Disease Control and Prevention, China Centre for Disease Control and Prevention (https://map.hla.cn/ )— among the 1,314 reported cases from Shandong Province in 2020, the resistance rates to clarithromycin, metronidazole, and levofloxacin were 65.14%, 94.52%, and 59.89%, respectively. In contrast, resistance to amoxicillin, tetracycline, and furazolidone was 0.30%, 0.00%, and 0.00%, respectively. A meta-analysis of primary antibiotic resistance to *H. pylori* in the Asia–Pacific region reported that the overall mean prevalence of primary *H. pylori* resistance was 17% (95% CI [15-18]) for clarithromycin, 44% (95% CI [39–48]) for metronidazole, 18% (95% CI [15-22]) for levofloxacin, 3% (95% CI [2-5]) for amoxicillin, and 4% (95% CI [2-5]) for tetracycline. The prevalence of resistance to clarithromycin and levofloxacin rose markedly over time during the investigative period, whereas resistance to other antibiotics remained stable [6]. A meta-analysis that reported the resistance patterns of *H. pylori* strains in the United States between 2011 and 2021 found that metronidazole, levofloxacin, and clarithromycin resistance rates each exceeded 30%, whereas resistance to tetracycline, rifabutin, and amoxicillin remained relatively low [7]. The efficacy of clarithromycin- and quinolone-containing regimens is highly affected by their resistance, and repeating these drugs in rescue treatments is discouraged [8, 9]. Therefore, it may be assumed that AST yields useful information regarding only clarithromycin and quinolone in clinical practice.

Choosing an antibiotic regimen with knowledge of the likely pattern of antibiotic resistance is generally preferred. However, a randomised control trial (RCT) recently reported that AST-guided therapy was not superior to personal medication history-guided therapy as a second- or third-line treatment for *H. pylori* infection [10]. Due to its cost-effectiveness, personal medication history-guided therapy is more clinically favourable than AST. A meta-analysis suggested that susceptibility-guided therapy (SGT) may be slightly superior to empirical first-line triple therapy; however, SGT does not appear to be superior to empirical first-line quadruple therapy or empirical rescue therapy [11]. Another meta-analysis revealed that, compared with bismuth-containing quadruple therapy (BQT), SGT showed similar efficacy to the first-line treatment of *H. pylori* infection in areas with high antibiotic resistance [12]. A limitation of RCTs is that many comparative studies evaluating SGT versus empirical treatment included susceptibility testing for only one antibiotic (clarithromycin); metronidazole susceptibility was assessed only in some cases, and quinolone resistance was only exceptionally evaluated [9]. Another limitation is the poor quality of clinical trials using unoptimised regimens and incomparable comparisons related to marked geographic heterogeneity [13]. A meta-analysis reported that the overall eradication rate in patients harbouring susceptible strains was 95.0% (95% CI [94.1–95.9]), but only 63.4% of treatment arms (64/101) achieved good eradication rates (≥ 90%) [14]. Furthermore, almost every RCT study on AST of *H. pylori* only included either first-line or rescue therapies [11, 12, 14–16].

In summary, although SGT is frequently recommended for *H. pylori* infection, the evidence available to date supporting this strategy is limited. Susceptibility testing alone seems insufficient to reliably attain high *H. pylori* eradication rates. The true utility of AST and its timing—before the first treatment or only after eradication failure—are both controversial.

In our study design, AST guides both the first-line and rescue therapies. A sequential strategy should focus not only on the first-line treatment, but also on a consecutive rescue treatment regimen after first-line failure. At the same time, the choice of treatment regimens should be based on local susceptibility, updated guidelines, and recent RCT results [17–20]. Clarithromycin resistance is the main factor to consider when deciding which regimen to use for *H. pylori* infections; thus, for the first-line treatment, we chose therapy regimens based on clarithromycin susceptibility. After first-line treatment failure, fluoroquinolone-containing quadruple (or triple) therapy may be recommended, as per the Maastricht VI/Florence consensus report [17]. Therefore, for the rescue treatment, we chose therapy regimens based on levofloxacin susceptibility. We hypothesise that, compared with empirical therapy, the susceptibility-guided sequential strategy will demonstrate a higher eradication rate for *H. pylori* infection.

## Objectives {7}

The main objective of this trial is to assess whether a sequential strategy based on molecular AST for *H. pylori* infection will have a better eradication rate than an empirical therapy (ET).

## Trial design {8}

This trial is designed as a prospective, single-centre, randomised, open-label, active-controlled equivalence study with a 1:1 allocation ratio. The study procedure is detailed in Fig. 1.

**Fig. 1 Fig1:**
[figure not shown]
Flowchart of the study. PPI: Proton-pump inhibitor

## Methods: participants, interventions, and outcomes

### Study setting {9}

The study will be conducted primarily in the outpatient clinic and endoscopic centre of Liaocheng People’s Hospital, which is a Class A comprehensive tertiary hospital in China.

### Eligibility criteria {10}

#### Inclusion criteria

18–65 years of age (including men and women).
*H. pylori*-positive, which will be determined using at least one of the following tests: 13C/14C-urea breath test (UBT), stool *H. pylori* antigen test, rapid urease test, and histological analysis within 4 weeks. Naïve to *H. pylori* treatment.

#### Exclusion criteria

 Allergic to any drug administered. Pregnant or lactating. Has major systemic diseases, such as severe cardiopulmonary or liver dysfunction. Diagnosed with active peptic ulcer disease within the past 8 weeks, history of gastric cancer, or prior gastrectomy.

### Who will take informed consent? {26a}

Participants must provide written informed consent before any study procedures occur. The investigators will explain and discuss the trial with the potential participants, confirm that they understand the research, and ensure that their agreement to participate is voluntary. The investigators will obtain written informed consent from the participants.

### Additional consent provisions for collection and use of participant data and biological specimens {26b}

Gastric mucosal samples will be stored for use in future studies. The original informed consent form includes information on data collection and request. Consent will be obtained from participants to use their data and specimens in future research unrelated to the clinical condition under study.

## Interventions

### Explanation for the choice of comparators {6b}

The ET group will receive BQT as a first-line treatment because the combination of amoxicillin and clarithromycin (74.8%) is the most commonly prescribed treatment in China [21] and has a high eradication rate for naïve patients. Moreover, antimicrobial resistance does not markedly affect its therapeutic efficacy [22]. The BQT regime comprises esomeprazole (20 mg, twice daily), colloidal bismuth pectin (150 mg, four times daily), clarithromycin (500 mg, twice daily), and amoxicillin (1.0 g, twice daily) taken for 14 days. If BQT fails, high-dose dual therapy (HDDT)—esomeprazole (20 mg, four times daily) and amoxicillin (750 mg, four times daily)—will be used as a rescue treatment for another 14 days. This regime was recommended by the Maastricht VI/Florence consensus [17]. Additionally, meta-analyses have reported that the HDDT regimen has better efficacy and safety in *H. pylori* eradication than current guideline-recommended regimens, particularly in Asia [20, 23]. The HDDT regimen does not rely on a susceptibility test, as the resistance rate to amoxicillin is extremely rare (< 5%), even after the failure of treatment, allowing it to be empirically prescribed.

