### Intervention description {11a}

The SGT group’s regimens will be selected according to *H. pylori* susceptibility to clarithromycin and levofloxacin. Participants will undergo an upper endoscopy to provide gastric mucosal samples for molecular testing. The test is based on polymerase chain reaction (PCR), which detects *H. pylori* mutations associated with clarithromycin and levofloxacin resistance. The susceptibility testing PCR protocol is outlined in Additional File 1. Regimens for the first-line treatments are based on clarithromycin susceptibility: If the *H. pylori* strain is sensitive to clarithromycin, we will administer clarithromycin triple therapy—esomeprazole (20 mg, twice daily), clarithromycin (500 mg, twice daily), and amoxicillin (1.0 g, twice daily)—for 14 days, as per the recommended guideline [17]. If the strain is clarithromycin resistant, we will administer the HDDT regimen because a network meta-analysis revealed that this treatment is the most optimal first-line therapy for *H. pylori* among the Asian population [24]. If the first-line treatment fails, rescue therapy will be selected according to levofloxacin susceptibility. If the *H. pylori* strain is levofloxacin sensitive, we will administer the levofloxacin quadruple regimen—esomeprazole (20 mg, twice daily), levofloxacin (500 mg, once daily), amoxicillin (1.0 g, twice daily), and colloidal bismuth pectin (150 mg, four times daily)—for 14 days, as per the recommended guideline [17]. If *H. pylori* is levofloxacin-resistant, we will administer the furazolidone quadruple regimen—esomeprazole (20 mg, twice daily), furazolidone (100 mg, twice daily), amoxicillin (1.0 g, twice daily), and colloidal bismuth pectin (150 mg, four times daily)—for 14 days. This furazolidone regimen can provide a satisfactory eradication rate in patients with multiple treatment failures and does not increase the incidence of adverse events [25, 26].

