## Statistical methods

### Statistical methods for primary and secondary outcomes {20a}

The eradication rate of *H. pylori* will be evaluated using ITT, mITT (including all participants who received at least one dose of the study drug), and per-protocol (PP) analyses (including participants who had good compliance and were re-examined by 13C-UBT). A point estimate and two-sided 95% CI of the difference in eradication rates between the SGT and ET groups will be calculated via the Miettinen & Nurminen method for the primary and secondary outcomes. Participants who have not undergone a re-examined 13C-UBT will be considered as treatment failures, i.e., ‘not eradicated,’ in the statistical analysis. Propensity score analysis will be used to adjust for differences in treatment regimens and potential confounding factors. Compliance and sensitivity analyses will be conducted to compare the treatment responses between compliant and non-compliant participants and determine if there is a significant association between compliance and treatment outcomes. Statistical significance will be set at *P* < 0.05.

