### Methods for additional analyses (e.g., subgroup analyses) {20b}

We plan to conduct a subgroup analysis that compares the *H. pylori* eradication rate between the clarithromycin resistance group and the empirical BQT failure group. Both groups are HDDT treatment regimens; the former is first-line treatment, and the latter is the rescue treatment. We anticipate that HDDT will be equally effective in both groups. A point estimate and a two-sided 95% CI of the difference in eradication rates between the two groups will be calculated via the Miettinen & Nurminen method. Statistical significance will be set at *P* < 0.05.

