The limitation of our study is that to obtain gastric biopsies for susceptibility testing, we require endoscopies, which are expensive, uncomfortable, and have a low acceptance rate by patients. Further studies into the development of more easily accessible methods of resistance testing, such as stool testing for the six commonly used antibiotics without the need for endoscopy, are required.

In summary, this randomised controlled trial will provide objective and valid evidence about the value of PCR-based molecular methods used for AST in guiding *H. pylori* eradication.

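### The planned propensity-score adjustment for treatment regimen should be removed from the between-arm analysis, because first-line regimen is the randomised intervention, and the closing conclusion should be limited to the strategy compared

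*Protocol article*

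**What the plan says.** All places are in the protocol article.

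- **Empirical arm ({6b}).** Everyone starts BQT (esomeprazole, bismuth, clarithromycin, amoxicillin). HDDT is the rescue. Of HDDT the section says "The HDDT regimen does not rely on a susceptibility test", and cites rare amoxicillin resistance as "allowing it to be empirically prescribed".
- **Guided arm ({11a}).** First-line is clarithromycin triple therapy for sensitive strains and HDDT for resistant strains. Rescue is levofloxacin or furazolidone quadruple therapy.
- **Analysis ({20a}).** Eradication is compared on ITT, mITT and per-protocol sets by a Miettinen & Nurminen difference with 95% CI. The section then adds: "Propensity score analysis will be used to adjust for differences in treatment regimens and potential confounding factors".
- **Additional analysis ({20b}).** Guided participants with resistant strains are compared with empirical BQT failures: "Both groups are HDDT treatment regimens; the former is first-line treatment, and the latter is the rescue treatment".
- **Objective ({7}).** "The main objective of this trial is to assess whether a sequential strategy based on molecular AST" eradicates better than empirical therapy.
- **Conclusion.** The Abstract promises "objective and valid evidence about the value of polymerase chain reaction-based molecular methods for antibiotic susceptibility testing" and the Discussion "objective and valid evidence about the value of PCR-based molecular methods used for AST". Both sentences go on to tie that value to guiding eradication.

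**The concern.** An adjustment for regimen in a trial that randomises between regimens treats the intervention as a confounder. First-line regimen is chosen after randomisation, as part of the strategy, and differs between arms by design. If the adjusted analysis is run and reported beside the primary estimate, readers will see either a failed model or a number that does not measure the strategy.

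The second matter is attribution. The guided arm differs from the empirical arm in two ways at first line: a test is done, and HDDT becomes available. By the protocol's own account HDDT could be given without the test. A sentence crediting the PCR method therefore says more than the contrast can show. The adjustment in {20a} could not separate the two either.

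**Working it through.** **1. Planning figures.** Inputs from {14}: 90% guided, 80% empirical, power 80%, two-sided alpha 0.05, dropout 20%.

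n per arm = (0.9×0.1 + 0.8×0.2) × (1.960 + 0.842)² / 0.10² = 196.2, so 197. With dropout, 197/0.8 = 246.3, so 247 per arm and 494 in total. The protocol's figures reproduce; the sample size is not at issue.

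**2. Overlap of first-line regimens ({6b}, {11a}).**

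| Regimen | Empirical | Guided | P(guided given regimen) |
|---|---|---|---|
| BQT | all | none | 0 |
| Triple | none | sensitive strains | 1 |
| HDDT | none | resistant strains | 1 |

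A propensity score that includes regimen is exactly 0 or 1 for everyone, so positivity fails. By method:

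- Matching finds no pairs, and no stratum contains both arms.
- The score used as a covariate is identical to arm.
- Overlap weights e(1 − e) are all zero.
- Inverse-probability weights, 1/e in the guided arm and 1/(1 − e) in the empirical arm, all equal 1, so the unadjusted difference comes back and nothing has been adjusted.
- In a regression with columns (intercept, arm, triple, HDDT), arm = triple + HDDT. The rank is 3 with 4 columns, so the arm effect is not estimable.

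**3. If software returns a number by dropping a regimen column.** The arm coefficient then becomes HDDT minus BQT or triple minus BQT, depending on the column dropped. For illustration, assume triple therapy cures 95%, 65.14% of strains are resistant, and the arms cure 90% and 80%. HDDT must then cure (0.90 − 0.3486×0.95)/0.6514 = 0.873. The two possible coefficients are 87.3 − 80 = 7.3 points and 95 − 80 = 15 points. The strategy effect is their weighted mean, 0.6514×7.3 + 0.3486×15 = 10.0, and neither coefficient equals it.

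**4. The comparison in {20b}.** Both groups receive HDDT, so there is no regimen difference to adjust for. They differ in line of therapy, prior failure and resistance status, and they are not randomised against each other.

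**5. Attribution.** Let p be the resistant proportion, T the triple cure rate in sensitive strains, and h the HDDT cure rate, assumed equal in both strata. Then 0.90 = p·h + (1 − p)·T. Test share = 0.90 − h (guided minus untested HDDT for all). Regimen share = h − 0.80.

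| T (assumed) | p | h | Test share | Regimen share |
|---|---|---|---|---|
| 0.90 | any | 0.900 | 0 | 10.0 |
| 0.95 | 0.6514 | 0.873 | 2.7 | 7.3 |
| 0.95 | 0.50 | 0.850 | 5.0 | 5.0 |
| 0.95 | 0.333 | 0.800 | 10.0 | 0 |

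The 65.14% is a provincial figure for reported cases ({6a}), not stated to be for treatment-naive patients. The 95.0% in {6a} is an overall rate in susceptible strains across regimens, so its use for triple therapy is an assumption. At the 17% regional resistance also in {6a}, T = 0.95 would force h = (0.90 − 0.83×0.95)/0.17 = 0.656, below BQT, so these inputs fit together poorly there. The table shows only that the shares are not identified; it does not estimate them.

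**The case against.** In a test-and-treat trial the test can act only by changing treatment, so different regimens between arms are the strategy. The objective is a strategy comparison, BQT is justified as common practice, and an untested HDDT comparator would be another trial. This stands: the trial answers its stated objective.

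The closing sentences speak of PCR testing in guiding eradication, which can be read as the whole strategy. That is fair, and it makes the attribution point smaller. The sentences still credit the method, and no arm or planned analysis isolates it.

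The propensity sentence does not replace the Miettinen & Nurminen difference, it also covers secondary outcomes, and an analysis plan not shown may define the model. The first part stands. The rest does not rescue the wording. First-line and rescue regimens both fail to overlap between arms, and in {20b} there is no regimen difference. No further model detail makes regimen a usable covariate in a between-arm comparison.

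Two stronger readings are tempting. A reader might infer that the test contributes little, since HDDT could explain most of a win. The documents give no regimen-specific planning rates, and the opposite split is equally compatible. A reader might also infer that the protocol concedes that endoscopy and PCR are both costly. The Discussion calls only endoscopy expensive and uncomfortable, and describes PCR as cost-efficient.

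**Conclusion.** The regimen adjustment in {20a} is wrong as written for the between-arm comparisons and should be corrected. This follows from the regimens in {6b} and {11a} and needs no numerical assumption. The damage is confined to the adjusted analysis.

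The attribution point is secondary and concerns the closing conclusion in the Abstract and Discussion. The trial can show whether the guided strategy beats empirical clarithromycin-amoxicillin BQT with HDDT rescue. It cannot show whether PCR testing adds anything over untested first-line HDDT. The size of the test's contribution cannot be determined from the documents. The 0-to-10-point range rests on assumed regimen rates and on equal HDDT efficacy in sensitive and resistant strains. It would be wrong to infer that the primary comparison is invalid or that testing has no value.

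**What to change.** 1. In {20a}, delete the adjustment for treatment regimens from all between-arm comparisons. Keep the unadjusted Miettinen & Nurminen ITT difference as the primary estimate. Use propensity scores at most for baseline confounders in the non-randomised HDDT comparison of {20b}. Cost: one sentence.
2. In the Abstract and Discussion, limit the conclusion to the guided sequential strategy versus empirical clarithromycin-amoxicillin BQT with HDDT rescue. State that the trial does not show whether PCR testing improves on untested first-line HDDT. Cost: wording, and a narrower conclusion.
3. Optional, if empirical-arm biopsies are PCR-tested ({33} reads as if every patient is sampled; {11a} describes endoscopy under the guided arm): report HDDT versus BQT in resistant strains and triple versus BQT in sensitive strains, as estimates with 95% CIs. With 250 per arm, triple at 95% and BQT at 80%, half-widths are about 8 to 12 points in resistant strains and 7 to 10 in sensitive strains.
4. Optional and exploratory: the guided-arm difference between triple and HDDT cure rates, multiplied by the proportion sensitive, with the equal-efficacy assumption stated.

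Neither optional analysis isolates the test's contribution, because first-line HDDT is never given for a sensitive strain. Regimens and sample size stay as they are.
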